### Interventions with study device and drug

The treatment strategy will be determined by the study-certified interventional operator. It is recommended that each enrolling investigator review the most recently updated instructions for use (IFU) and assess the contraindications, warnings, and precaution sections for treating potential patients. Direct stenting or predilation, antithrombotic medications during the procedure, and use of glycoprotein IIb/IIIa inhibitors will be left to the operator’s discretion.

The PtCr-EES (Promus Premier^TM^) is available in diameters of 2.25, 2.5, 2.75, 3.0, 3.5 and 4.0 mm with lengths of 12, 16, 20, 24, 28, 32 and 38 mm (2.25 mm diameter not available for 38 mm lengths). The BP-BES (Biomatrix®, Biomatrix Flex®) is available in diameters of 2.25, 2.5, 2.75, 3.0, 3.5 and 4.0 mm with lengths of 8, 11, 14, 18, 24, 28, 33 and 36 mm (33 and 36 mm lengths not available for 2.25 and 4.0 mm of diameters). Another BP-BES (Nobori®) is available in diameters of 2.25, 2.5, 2.75, 3.0 and 3.5 mm with lengths of 8, 14, 18, 24 and 28 mm. The allocated stent from the randomization should be implanted in all lesions treated. However, other stents may be used in case of device failure or situations in which the operators decide considering the best interest of the patient. It is recommended to make two attempts to cross the lesion with the allocated stent before switching to another stent. Complete lesion coverage is recommended. In case of long lesions, stent overlap of 1 to 4 mm will be recommended per IFU. The use of intravascular ultrasound, fractional flow reserve or optical coherence tomography will be left to the clinician’s discretion.

All patients will receive 300 mg of aspirin and a loading dose of prasugrel intravenously before performing PCI. Patients excluded from antiplatelet comparison will receive other P2Y12 inhibitors including clopidogrel, and ticagrelor. Patients included in the antiplatelet comparison will maintain aspirin with 10 mg of prasugrel until 1-month follow-up. After a 1-month period, patients randomized to the conventional dose group will receive a 10-mg daily dose of prasugrel, and the reduced group will receive a 5-mg daily dose. Dual antiplatelet therapy will be recommended for at least 1 year. The antiplatelet agent, however, could be adjusted at the clinician’s discretion in patients with bleeding events.

After the 1-year follow-up visit, the patient could discontinue one of the dual antiplatelet agents in accordance with clinician’s discretion. Thus, we could evaluate the rebound phenomenon beyond 1 year after change of prasugrel to clopidogrel, as well as the clinical outcome in the chronic phase when the polymer has completely gone in the BP-BES.

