**Method/Design:**

Harmonizing Optimal Strategy for Treatment of coronary artery diseases – comparison of REDUCtion of prasugrEl dose or POLYmer TECHnology in ACS patients (HOST-REDUCE-POLYTECH-ACS) trial is a multicenter, randomized and open-label clinical study with a 2 × 2 factorial design, according to the type of stent (PtCr-EES versus BP-BES) and prasugrel maintenance dose (5 mg versus 10 mg), to demonstrate non-inferiority of PtCr-EES relative to BP-BES or the reduced prasugrel dose relative to conventional dose in an Asian all-comers PCI population presenting with ACS. Approximately 3400 patients will undergo prospective, random assignment separately to either stent or prasugrel arm (1:1 ratio, respectively). When the patients have contraindications to prasugrel, they are categorized into an antiplatelet observation group after stent-randomization. The primary endpoint is the patient-oriented composite outcome, which is a composite of all-cause mortality, any myocardial infarction (MI), any repeat revascularization in the stent arm at 12 months after index PCI. In the prasugrel arm, primary endpoint is any major adverse cardiovascular event, which is a composite of all-cause mortality, any MI, any stent thrombosis (Academic Research Consortium (ARC)-defined), any repeat revascularization, stroke, or bleeding (BARC class ≥ 2).

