In this study, we will compare 2 different maintenance doses of prasugrel beyond 1 month after PCI: conventional dose of 10 mg versus a reduced dose of 5 mg of prasugrel in Asian patients with ACS undergoing PCI. All of the enrolled patients will receive the currently recommended loading dose of prasugrel (60 mg), and maintain a 10-mg daily dose for the first month. After 1-month clinical follow-up, patients will receive maintenance dosage randomly assigned after PCI (10 mg versus 5 mg). Dual antiplatelet therapy is recommended for at least 1 year. Clinical adverse events, including bleeding, will be compared at 1-year clinical follow-up.

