### Study population and entry criteria

ACS patients with at least 18 years of age who meet all of the inclusion criteria (Table 1) are eligible for this study. Patients must have a culprit lesion in a native coronary artery or a graft vessel with significant stenosis (>50 % by visual estimate) eligible for stent implantation as in the current recommendations of ACC/AHA/SCAI and ESC/EACTS guidelines [4, 23]. Patients with known hypersensitivity or contraindication to heparin, aspirin, clopidogrel, prasugrel, ticagrelor, biolimus, everolimus, or contrast media will be excluded. Additional exclusion criteria will be systemic (intravenous) biolimus, or everolimus use within 12 months, with active pathologic bleeding, with gastrointestinal or genitourinary bleeding within the prior 3 months, women of childbearing potential, history of bleeding diathesis, known coagulopathy (including heparin-induced thrombocytopenia), or refused blood transfusions, presence of non-cardiac co-morbid conditions with life expectancy less than 1 year or conditions that may result in protocol non-compliance. Inclusion and exclusion criteria will be graded to minimize exclusion of patients, thus reflecting a population at-large.

**Table 1 Tab1:** Enrollment criteria

General inclusion criteria
1. Subject must be ≥ 18 years
2. Subject is able to verbally confirm understandings of risks, benefits and treatment alternatives of receiving percutaneous coronary intervention and he/she or his/her legally authorized representative provides written informed consent prior to any study related procedure
3. Subject must have a culprit lesion in a native coronary artery with significant stenosis (>50 % by visual estimate) eligible for stent implantation
4. Subject must have clinical diagnosis of acute coronary syndrome that includes unstable angina (crescendo, new-onset, resting) and myocardial infarction
Exclusion criteria
● The following patients will be enrolled in stent comparison, but excluded from antiplatelet prasugrel comparison. They will be classified as antiplatelet observational cohort:
1. Subjects ≥ 75 years
2. Body weight < 60 kg
3. History of TIA or stroke

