1. The patient has a known hypersensitivity or contraindication to any of the following medications: heparin, aspirin, clopidogrel, prasugrel, ticagrelor, biolimus, everolimus, contrast media (patients with documented sensitivity to contrast media (e.g. rash) who can be effectively premedicated with steroids and diphenhydramine] may be enrolled. Those with true anaphylaxis to prior contrast media, however, should not be enrolled)
2. Patients with active pathologic bleeding
3. Gastrointestinal or genitourinary bleeding within the prior 3 months, or major surgery within 2 months
4. Systemic (intravenous) biolimus, or everolimus use within 12 months
5. Woman of childbearing potential, unless a recent pregnancy test is negative, who possibly plans to become pregnant any time after enrollment into this study
6. History of bleeding diathesis, known coagulopathy (including heparin-induced thrombocytopenia), or will refuse blood transfusions
7. Non-cardiac co-morbid conditions are present with life expectancy < 1 year or that may result in protocol non-compliance (per site investigator’s medical judgment)

*TIA* transient ischemic attack

If all eligible criteria are met and written informed consent is provided, patients will be randomized 1:1 to either (a) PtCr-EES or (b) BP-BES group, and 1:1 to either (a) reduced dose of prasugrel (5 mg daily) or (b) the conventional dose (10 mg daily) group. Patients who meet the exclusion criteria of prasugrel (age ≥ 75 years, body weight < 60 kg, or history of transient ischemic attack or stroke) will be enrolled in stent comparison, but excluded from prasugrel comparison. To generate comparable groups relative to known and unknown risk factors, randomization will be independently conducted online (T&W Software, Seoul, Korea) via web-based application. All randomization will be balanced, stratified by participating center and allocated treatment groups. According to the consideration of calculated sample size to meet non-inferiority in each comparison arms, a total of 3384 patients from 22 centers in Korea will be planned to be enrolled.

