### Limitations

The possible expected limitations of the current trial should be acknowledged. Firstly, we set the statistical power of the prasugrel arm as 75 %. About 30 % of the stent comparison arm would not be enrolled in the prasugrel arm due to several factors (absolute or relative contraindication of prasugrel use, or other clinical circumstances including high risk of bleeding); therefore, sample size of prasugrel arm will be inevitably lower than stent comparison arm. With the limited sample size of the stent comparison arm, it was considered to be difficult to further enhance statistical power of the prasugrel arm in contemporary practice in Korea.

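### The loading drug for the stent-only cohort is contradictory, and patients with a prasugrel contraindication outside the three named criteria are both excluded and enrolled

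*Protocol article*

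**What the plan says.** **Loading treatment.** The protocol article, under Interventions with study device and drug, states: "All patients will receive 300 mg of aspirin and a loading dose of prasugrel intravenously before performing PCI". The sentence immediately after it reads: "Patients excluded from antiplatelet comparison will receive other P2Y12 inhibitors including clopidogrel, and ticagrelor".

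**Who is outside the antiplatelet comparison.** Table 1 lists three criteria: age 75 or over, weight under 60 kg, and previous TIA or stroke. It says these patients enter the stent comparison only and form an antiplatelet observational cohort. The text after the table repeats this, and Sample size calculations uses the same three criteria for its expected 30 %.

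**Contraindication to prasugrel.** The text of Study population and entry criteria says: "Patients with known hypersensitivity or contraindication to heparin, aspirin, clopidogrel, prasugrel, ticagrelor, biolimus, everolimus, or contrast media will be excluded". Item 1 of the second list in Table 1 gives the same criterion: "The patient has a known hypersensitivity or contraindication to any of the following medications: heparin, aspirin, clopidogrel, prasugrel, ticagrelor, biolimus, everolimus". The abstract (Method/Design) says something different: "When the patients have contraindications to prasugrel, they are categorized into an antiplatelet observation group after stent-randomization". The Limitations section agrees with the abstract. It explains why about 30 % of the stent arm will not be in the prasugrel arm by "absolute or relative contraindication of prasugrel use, or other clinical circumstances including high risk of bleeding".

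**The concern.** There are two separate conflicts.

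The first concerns treatment. The loading sentence covers every patient, including those the plan keeps out of the prasugrel comparison. The following sentence gives those same patients a different P2Y12 inhibitor. It contains no exception, no replacement and no sequence such as a load followed by a switch. A site following the text cannot tell whether a stent-only patient is to be loaded with prasugrel. The article's own Background and Discussion cite guidelines that treat higher age, low body weight and previous TIA or stroke as exceptions to the preference for prasugrel, so the ambiguity matters for safety.

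The second concerns eligibility. The same word, contraindication, bars a patient from the trial in one place and admits the patient to the stent comparison in another. Sites could apply different entry rules, and the population of the stent comparison would then not be described consistently. Recruitment began in October 2014 according to Trial status, so different readings may already be in use.

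**Working it through.** **Step 1. Size of the stent-only cohort.** Inputs: 3384 patients in total (Study population and entry criteria; Sample size calculations), and 30 % expected outside the prasugrel comparison (Sample size calculations).

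- Prasugrel comparison: 3384 × (1 − 0.30) = 2368.8, rounded to 2369. This reproduces the plan's stated 2369.
- Stent-only cohort: 3384 × 0.30 = 1015.2, about 1015.
- Check: 2369 + 1015 = 3384.

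The plan's arithmetic is consistent: it counts the stent-only patients in the 3384 and leaves them out of the 2369.

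**Step 2. Apply the text to two kinds of patient.**

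| Patient | Question | One statement | Other statement |
|---|---|---|---|
| Meets one of the three named criteria | Enrolled? | Stent comparison only (Table 1 and the text after it) | Same in Sample size calculations |
| Meets one of the three named criteria | Loading drug? | Prasugrel (Interventions, loading sentence) | Another P2Y12 inhibitor (Interventions, next sentence) |
| Has another known prasugrel contraindication | Enrolled? | Excluded (entry criteria text; Table 1, second list, item 1) | Stent-randomized and observed (abstract; in substance, Limitations) |

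The first row is consistent. The second and third are not.

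**Step 3. Is the scope of the loading sentence limited elsewhere in its section?** The sentence on first-month maintenance in the same paragraph is expressly limited to patients in the antiplatelet comparison. The loading sentence has no such limit. The conflict therefore lies within that one paragraph and needs no support from other sections.

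**Step 4. How many patients does the eligibility conflict affect?** It affects only patients whose prasugrel contraindication falls outside the three named criteria. The documents give no frequency for them, so no number can be calculated. The figure of 1015 belongs to the loading conflict alone.

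**The case against.** The strongest defence of the loading text is that a general statement is followed at once by its exception, and that investigators would read it so. That reading is plausible, but the second sentence is not worded as an exception and does not mention loading. It would be equally satisfied by a prasugrel load followed by another agent. The defence shows what may have been meant; it does not remove the ambiguity.

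On eligibility, the defence is that the three named criteria lead to stent-only enrolment and every other contraindication leads to exclusion. Table 1 makes this a natural split, and it stands for the three groups. For other contraindications the article never states the split, and the abstract and Limitations speak against it. The second list in Table 1 appears without a heading in the available text. A heading may have been lost, but the prose exclusion does not depend on it.

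Three stronger readings are tempting, and the documents do not support them.

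- A reader might infer that the exclusion rule makes the whole observational cohort ineligible and shrinks the stent comparison to 2369. Table 1, the text after it and Sample size calculations all expressly enrol the three groups, which rules this out.
- A reader might count the Background and Discussion as further statements that everyone is loaded: "All of the enrolled patients will receive the currently recommended loading dose of prasugrel". In both places that sentence goes on to the 10-mg first-month regimen and leads to the assigned maintenance dose. It describes only patients in the dose comparison.
- A reader might add the route of administration in the loading sentence as a contradiction. No other section states a route for the load, so nothing in the article conflicts with it, and checking it would need a source outside the documents.

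**Conclusion.** The point holds in two limited parts.

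1. The loading drug for the stent-only cohort is contradictory between two adjacent sentences in the section that governs treatment. On the plan's own assumption of 30 %, this concerns about 1015 of 3384 patients. That figure is the number of patients whose instruction is unclear, not a count of patients who would be wrongly treated.
2. A known prasugrel contraindication other than the three named criteria leads to exclusion under the entry criteria and to enrolment under the abstract and Limitations. The size of this group is unknown.

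Neither part alters the sample size, the planned stent total of 3384 or the expected 2369 in the prasugrel comparison. The defect is one of conflicting instructions and not of design. It still needs correcting, because the first part bears on patient safety and the second on who may be randomized.

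**What to change.** The clinical leads should make two reconciliations.

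- **Interventions with study device and drug:** reconcile the loading sentence with the one after it, stating which patients the prasugrel load covers and what applies at loading to patients outside the antiplatelet comparison.
- **Abstract, entry criteria text, Table 1 and Limitations:** use one consistent statement of how a prasugrel contraindication is handled, and say how it relates to the three named criteria, so that no patient is both excluded from the trial and enrolled in its stent comparison.

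This should go to sites as a protocol clarification with a covering letter. The cost is small: no change to sample size, randomization or data collection. Which loading rule and which eligibility rule are right is for the clinical leads to decide; this review proposes neither.

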### Outcome measurements and definitions

There are two primary endpoints in this study. In the stent comparison arm, the primary endpoint will be POCO, defined as a composite of all-cause death, nonfatal MI, and any repeat revascularization at 12 months. In the prasugrel dose comparison arm, the primary endpoint will be MACE, defined as a composite of all-cause death, nonfatal MI, ST, repeat revascularization, CVA, and BARC class ≥ 2 bleeding at 12 months. Revascularization is considered clinically driven with follow-up angiographic diameter stenosis ≥ 50 %, and at least one of the following: 1) history of recurrent angina pectoris, presumably related to the target vessel; 2) objective signs of ischemia at rest or during exercise testing (or equivalent), presumably related to the target vessel; 3) abnormal invasive functional diagnostic testing; or 4) target lesion or target vessel revascularization with ≥ 70 % diameter stenosis, even without aforementioned ischemic signs/symptoms [24, 25]. To reduce the chance of so-called “oculostenotic reflex,” whereby rates of repeated revascularization are disproportionately high, investigators will be recommended to perform a non-invasive stress test prior to the decision of the re-intervention of the target lesions as much as possible and they will adhere strictly to a clinically driven revascularization protocol. All clinical outcomes were defined according to the Academic Research Consortium (ARC) [25, 26]. All clinical events including revascularization will be independently adjudicated by an independent event adjudication committee, and only clinically driven revascularization will be coded as an event.

Secondary endpoints will be the individual components of the primary endpoints. In addition, POCO and MACE rate at 36 months, device-oriented composite endpoint (composite of cardiac death, target vessel MI, or target lesion revascularization), and acute procedure success (device, lesion and procedure) will be included as secondary endpoints. In prasugrel the comparison arm, adherence to the study dose of prasugrel, PRU value by VerifyNow P2Y12 at 1 month, 12 months, and the ratio of patients with the therapeutic range of P2Y12 reaction units (PRU, 86-238) will also be analyzed [27].

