#### Statistical analyses

All primary and secondary endpoints and serious adverse events will be analyzed after adjudication by a member of researchers or clinicians. All primary and secondary endpoints will be analyzed both on an intention-to-treat basis (all patients analyzed as part of their assigned treatment group), and per-protocol basis. For patients receiving multi-vessel PCI, the target lesion/vessel will be declared by the operator prior to the interventional procedure.

Primary endpoints will be analyzed firstly on an intention-to-treat basis (all patients analyzed as part of their assigned treatment group), and then, on a per-protocol basis at 12 months and 3 years after index procedure. The null hypothesis will be evaluated on a non-inferiority basis with Kaplan-Meier survival with the log rank test. Non-inferiority is defined by a 1-sided alpha of 2.5 % and a difference in net POCO rates of less than 2 % in the stent comparison arm and MACE rate of less than 2.5 % in the antiplatelet comparison arm. All primary and secondary endpoints will be analyzed on a per-patient basis. Events within the first month, the period receiving a 10-mg dose of prasugrel before taking the allocated prasugrel dose, will also be analyzed on an intention-to-treat basis. In addition, a landmark analysis will be performed at 1 month after index PCI, as a sensitivity analysis.

Device-oriented composite endpoint (target lesion failure: a composite of cardiac death, target-vessel MI, or target lesion revascularization) will be analyzed using the *χ*^2^-test and Kaplan-Meier survival with the log rank test. Other secondary endpoints including all-cause and cardiac death, target vessel/lesion revascularization, non-target vessel/lesion revascularization, any revascularization, target-vessel and all-cause (including non-target vessel) nonfatal MI, ST, stroke (ischemic or hemorrhagic), bleeding (BARC classification ≥ 2) will be analyzed using the *χ*^2^-test and Kaplan-Meier survival with the log rank test. Acute procedure success (device, lesion, and procedure) and adherence to study dose of drug (prasugrel) will be analyzed using the *χ*^2^-test. The baseline coronary angiographic characteristics will be analyzed on a per-lesion basis.

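### The 3-year MACE comparison by prasugrel dose, intention-to-treat and per protocol, falls under a non-inferiority margin not limited to 12 months, although a dose contrast is assured only for months 1 to 12

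*Protocol article*

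**What the plan says.** Under Interventions with study device and drug, both prasugrel groups take 10 mg until the 1-month visit, and the allocated doses differ only after that. On duration the section says: "Dual antiplatelet therapy will be recommended for at least 1 year". After the 1-year visit, at the clinician's discretion, "the patient could discontinue one of the dual antiplatelet agents". The same section gives a purpose for the later follow-up in the dose arm: "we could evaluate the rebound phenomenon beyond 1 year after change of prasugrel to clopidogrel".

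Outcome measurements and definitions sets the primary endpoints at 12 months and lists "POCO and MACE rate at 36 months" as secondary.

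Statistical analyses starts with an intention-to-treat analysis of the primary endpoints. A second analysis follows, which the section places "on a per-protocol basis at 12 months and 3 years after index procedure". The next sentences describe a non-inferiority evaluation by Kaplan-Meier and log-rank methods, with a one-sided alpha of 2.5 % and a MACE margin of 2.5 points. They neither confine that rule to 12 months nor give a separate 3-year margin. The only landmark named is at 1 month.

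**The concern.** Read as written, the plan carries the dose comparison to 3 years in both analysis sets, under a margin set alongside 12-month event rates. Three things follow.

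- **Contrast.** From month 12 nothing in the plan keeps the groups on different doses. Departure from the allocated dose is an open-label clinical choice, so its timing and frequency may differ by arm.
- **Per-protocol set.** A patient who stops or switches after 1 year is acting within the protocol. Keeping such patients means the set is no longer an on-dose set. Removing them selects on a decision made after randomisation.
- **Interpretation.** In a non-inferiority setting, follow-up without contrast moves a ratio measure toward 1. A 3-year statement that the reduced dose is non-inferior could be taken as evidence on 3 years of maintenance dosing, which the design does not provide.

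The plan already adds a landmark for the first month, when both groups take 10 mg. It states no corresponding split for the much longer period after month 12.

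**Working it through.** **Assured contrast.** Month 1 to month 12 is 11 months, and 11/36 = 31 %. Months 12-36 are 24/36 = 67 %.

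**Inputs from the protocol article.** Conventional-dose MACE 8 % and reduced-dose MACE 7 % at 12 months; margin 2.5 points; one-sided alpha 2.5 %; 2348 patients 1:1, so 1174 per arm. The plan gives no 36-month rate or calculation, so there is no figure of its own to reproduce on this point. Its 75 % power for 2348 patients does not come out of the formula below, which gives 90 % at 7 % v 8 %. That is a separate matter and does not affect what follows.

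**Assumptions, not in the protocol.** After month 12 everyone leaves the allocated dose, and the yearly risk L is the same in both arms, 3-5 %. The margin case sets the reduced dose at 8 + 2.5 = 10.5 %.

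**Formulas.**
- 36-month risk = 1 − (1 − p12)(1 − L)²
- Hazard ratio = ln(1 − p reduced) / ln(1 − p conventional)
- SE = √{[p1(1 − p1) + p2(1 − p2)] / 1174}
- Chance of declaring non-inferiority = Φ[(0.025 − difference)/SE − 1.96]

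**Margin case.**

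| | 12 months | 36 months, L = 3 % | 36 months, L = 5 % |
|---|---|---|---|
| Conventional dose | 8.0 % | 1 − 0.92 × 0.9409 = 13.44 % | 1 − 0.92 × 0.9025 = 16.97 % |
| Reduced dose | 10.5 % | 1 − 0.895 × 0.9409 = 15.79 % | 1 − 0.895 × 0.9025 = 19.23 % |
| Difference (points) | 2.50 | 2.35 | 2.26 |
| Hazard ratio | 1.33 | 1.19 | 1.15 |
| SE (points) | 1.19 | 1.46 | 1.59 |
| Share of events after month 12 | – | 37 % | 49 % |
| Chance of declaring non-inferiority | 2.5 % | 3.2 % | 3.5 % |

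The risk difference keeps 94 % (L = 3 %) or 90 % (L = 5 %) of its 12-month value.

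**Same inputs, other truths.** At the planned 7 % v 8 %, the chance of declaring non-inferiority falls from 90 % at 12 months to 70 % (L = 3 %) or 60 % (L = 5 %) at 36 months. At 8 % v 8 % it falls from 61 % to 43 % or 36 %. With a fixed absolute margin, the larger SE makes the claim harder when the reduced dose is as good or better.

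**If fewer patients leave the dose (margin case).** The late hazard in the reduced arm is multiplied by 1.33 for those who stay on the dose and by 1 for those who leave.
- Half leave (average multiplier 1.165): hazard ratio 1.26-1.24, difference 3.2-3.6 points for L = 3-5 %.
- None leave: hazard ratio 1.33, difference 4.0-4.9 points, chance of declaring non-inferiority at most 0.2 %.

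The 3-year result thus depends heavily on a share that the protocol neither fixes nor predicts.

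**The case against.** A reader might infer that the 3-year dose result is mostly not about the dose and is pulled toward no difference. The documents do not support that.

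- Stopping after 1 year is permitted, not required. The agent stopped may be aspirin, and dual therapy has no upper time limit. The 31 % is therefore a minimum.
- Even with complete departure and equal late risk, 51-63 % of events fall before month 12, and the whole 36-month difference arises there. Only calendar time supports the word mostly.
- The margin is on the rate-difference scale, where shrinkage is small and the error rate moves only from 2.5 % to about 3.5 %.
- Rebound after a change to clopidogrel, which the authors want to study, could move the result in either direction.
- The 36-month intention-to-treat result remains a valid randomised comparison of initial dose strategies. The hypothesis and sample size are set at 12 months, and 36-month MACE is secondary.

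All of this stands, and it limits the size of the problem.

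It can also be said that per-protocol rules and an extra landmark belong in the statistical analysis plan, which is not shown. That is fair: their absence alone would be no finding. But the article itself fixes per-protocol analysis at 3 years and states a margin without a time limit. Those statements need correcting wherever the detail is kept.

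**Conclusion.** The point holds in a limited form. As written, the plan applies intention-to-treat and per-protocol analyses of MACE by dose at 3 years, under a margin not confined to 12 months, while assuring a dose contrast for only 11 of 36 months. A per-protocol dose set after month 12 has no clear meaning, and a 3-year non-inferiority claim about the maintenance dose would go beyond the design.

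The sizes in the working are illustrative. They rest on an assumed late risk of 3-5 % per year and, in the main case, on everyone leaving the allocated dose at month 12. Under those assumptions dilution is marked on the hazard-ratio scale and small on the risk-difference scale. The larger gap is between what would be observed (about 2.3 points) and what 3 years on the allocated doses would show at the same hazard ratio (4.0-4.9 points). The change should be made; the 12-month primary conclusion does not depend on it.

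**What to change.** In Statistical analyses:

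1. State that the 2.5-point MACE non-inferiority test and the per-protocol dose analysis apply at 12 months only.
2. Keep 36-month MACE by assigned dose, intention-to-treat, as a secondary comparison of initial dose strategies, with no non-inferiority claim about the maintenance dose.
3. Add a landmark at 12 months. Report events to month 12 and events in months 12-36 separately, the latter as descriptive because it is conditional on status at month 12. Show the antiplatelet agent actually taken in that period by arm. This also gives the rebound question a clock that starts where the change of agent may occur.
4. Leave the 36-month POCO comparison of stents as it is, since that allocation is permanent.

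The cost is a few sentences and one added analysis split. The sponsor gives up a 3-year non-inferiority claim for the dose. No treatment rule changes.
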